### Outcome assessment

All follow-up assessments will take place during outpatient clinic visits at 2 weeks, 6 weeks, 3 months, 6 months and 1 year. At each clinic visit, a physical examination will be performed, complications noted and the need for any further surgery recorded. Patients will be given time to complete a self-reported questionnaire, which will generate clinical outcome scores. The 1-year follow-up will enable study investigators to assess whether any differences between the operative and non-operative groups (if any) are sustained for 1 year post-intervention and to detect any important complications that may occur within the first year (e.g. nonunion).

The Standard Protocol Items: Recommendations for Interventional Trials (SPIRIT) [27] checklist is given in Additional file 1. The SPIRIT schedule of enrolment, interventions and assessments is shown in Fig. 3.

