### Power calculation and statistical analysis

Prior to study commencement, a prospective power calculation was used to determine the number of patients required in each treatment group. The minimal clinically important difference in the DASH score is reported to be 10 points [32], and the assumed standard deviation is 12 points for both the operative and non-operative groups [33]. Thus, using a two-sided *t*-test with 5% significance, a total of 70 patients (35 in each group) are required to produce a 90% power to detect a meaningful difference (in terms of the DASH score at 3 months post-intervention) between the two groups, assuming a 10% loss to follow-up.

Data will be analysed on an intention-to-treat basis. Data analysis will be performed by a senior statistician, employed by the local clinical research facility and independent of the study team. The primary outcome measure (DASH score at 3 months post-intervention) will be compared between the two treatment arms, using a two-sided independent samples *t*-test or non-parametric equivalent (as indicated by the normality of the data). This method will also be used to compare the other continuous outcome measures between the two treatment arms (e.g. pain score, satisfaction scores, shoulder and elbow range of motion, EQ-5D score and SF-12 score). The pattern of change in continuous outcome measures over the study period will be presented graphically, broken down by treatment allocation. A linear regression model will be generated for each participant by plotting the DASH score from 6 weeks to 1 year post-intervention and the gradient of the regression line (i.e. the rate of change in the score) will be compared between treatment groups. Multivariate linear regression, including analysis of covariance (ANCOVA), will also be used to adjust for the potential effect of pre-injury DASH score, age and other prognostic factors affecting the DASH score. Binary outcomes (e.g. treatment complications, re-operation and nonunion or malunion) will be compared between the two treatment arms using a binomial test for the comparison of proportions. Two-tailed *p* values will be reported where possible, and statistical significance will be set at *p* = 0.05.

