### Missing data

The study sample size has been increased to provide for up to 10% loss to follow-up at the primary outcome timepoint (3 months post-intervention). All clinical and outcome data will be collected in the outpatient clinic, where clinical reviews and radiographs (where required) are also performed. These appointments reflect routine follow-ups of a humeral shaft fracture in the study centre, and the investigators anticipate this arrangement will limit missing data considerably. The participant dropout rate for each treatment arm will be reported and compared. If the participant dropout rate at the primary outcome timepoint is substantial, a sensitivity analysis may be performed. Missing data at other timepoints will be accounted for by plotting a line of best fit for the data points for each participant and comparing the gradient of the regression line (i.e. the rate of change in the variable of interest) between treatment groups.

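### Comparing individual straight-line gradients cannot show whether a DASH difference is sustained at 1 year, and as the missing-data rule it can add bias when recovery is curved and late loss differs between arms

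*Protocol article*

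**What the plan says.** Two sections of the protocol article prescribe the same method.

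- *Power calculation and statistical analysis*, for change in DASH: "A linear regression model will be generated for each participant by plotting the DASH score from 6 weeks to 1 year post-intervention". The gradients of these lines are then compared between arms.
- *Missing data*, for every timepoint except 3 months: "Missing data at other timepoints will be accounted for by plotting a line of best fit for the data points for each participant". Again it is the gradient that is compared, for whichever variable is of interest.

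Neither section mentions weighting, a minimum number of visits, curvature, or an assumption about why data are missing. Dropout at 3 months is treated separately, with a sensitivity analysis that is only a possibility.

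*Outcome assessment* sets visits at 2 weeks, 6 weeks, 3 months, 6 months and 1 year. It says that the 1-year follow-up is there to "assess whether any differences between the operative and non-operative groups (if any) are sustained for 1 year post-intervention". Change in DASH over the year is the first secondary outcome listed.

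**The concern.** The question set for the 1-year follow-up is about level: is one arm still better at 1 year? A gradient measures only the rate of change. It is the only between-arm test specified for the course of DASH after 3 months, and DASH at 1 year is not explicitly listed for a comparison of levels. A sustained benefit could therefore go undetected by this analysis, or an arm that merely catches up could be read as the better one.

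The second issue is the use of the gradient to account for missing visits. If recovery is fast early and then flattens, a line fitted without the late visits is steeper than one fitted to all of them. Missing the 1-year visit then changes what the slope estimates as well as its precision. If more 1-year visits are missing in one arm, the arms can appear to differ when they do not.

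**Working it through.** **The plan's own figure.** Inputs from *Power calculation and statistical analysis*: "The minimal clinically important difference in the DASH score is reported to be 10 points"; "the assumed standard deviation is 12 points for both the operative and non-operative groups"; 90% power, "using a two-sided *t*-test with 5% significance"; 10% loss.

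n per arm = 2 × SD² × (z₀.₉₇₅ + z₀.₉₀)² / difference² = 2 × 144 × (1.960 + 1.282)² / 100 = 30.3, rounded up to 31. Then 31 / 0.9 = 34.4, rounded up to 35 per arm and 70 in total. This matches the plan. (The t-distribution version gives 32, then 36 per arm and 72 in total.) Nothing below changes this figure, because it concerns DASH at 3 months only.

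**Assumptions for the rest.** The article gives no mean DASH path, no within-person SD and no 1-year loss rate, so all of these are assumed. Visit times are 6 weeks = 6 / 4.345 = 1.38 months, then 3, 6 and 12 months. Each slope is Σ(t − t̄)y / Σ(t − t̄)².

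With all four visits, t̄ = 5.595, the deviations are −4.214, −2.595, 0.405 and 6.405, and Σ(t − t̄)² = 65.68.

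**Step 1: level against gradient, no missing data.**

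- Constant gap: adding 10 to every score leaves Σ(t − t̄)y unchanged, because the deviations sum to zero. The slope difference is 0. In simulation the test rejects in about 5% of runs, so a sustained benefit equal to the plan's own minimal important difference is invisible.
- Converging arms: assumed means of 35/22/14/10 (operative) and 50/32/17/11 (brace) give −134.9 / 65.68 = −2.05 and −216.4 / 65.68 = −3.30 points per month. Operative is better at every visit, yet the brace has the steeper slope. The slope test is significant in 99.9% of runs.

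**Step 2: effect of losing the 1-year visit on one curve.** Take 45/28/16/11. All four visits give −2.82. Without 12 months, t̄ = 3.460, Σ(t − t̄)² = 10.99 and the slope is −5.99.

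**Step 3: false positives with identical arms.** Simulation: 35 per arm, between-person SD 9, residual SD 8, the 1-year visit missing at random within each arm, t-test on unweighted slopes.

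| Missing at 1 year | 45/28/16/11 | 38/25/16/12 | 32/24/17/12 |
|---|---|---|---|
| Equal in both arms (up to 20%) | about 5% | about 5% | about 5% |
| 5% v 10% | 7% | 6% | 5% |
| 5% v 20% | 22% | 16–17% | 9% |
| 10% v 30% | 29% | 21% | 12% |

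In a further run with truly linear paths, losing late visits at 10% v 30% gave 5.6%. The bias therefore needs both curvature and unequal loss.

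**Step 4: precision.** The SE of one participant's slope is residual SD / √Σ(t − t̄)². With residual SD 8:

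- four visits: 8 / √65.68 = 0.99;
- first three: 8 / √10.99 = 2.41;
- first two: 8 / √1.31 = 6.99.

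The variance ratios to the full-data slope are 1, 6.0 and 50. If slopes are compared unweighted, all of these count equally. A participant with one visit has no slope.

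**The case against.** The case for leaving the plan alone has substance.

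- **Only secondary analyses are at stake.** The 3-month t-test and its dropout allowance do not use slopes. This stands, and a reader who infers that the primary result is compromised would be wrong.
- **The gradient is labelled as a rate of change.** The article never says that a steeper slope means a better treatment, and in the converging example the brace arm really does change faster. This stands as far as it goes: the danger is misreading. It does not help with the 1-year question, which a rate cannot answer.
- **Other analyses soften the harm.** Other continuous outcomes are also compared by t-test or a non-parametric test, courses over time are graphed by arm, ANCOVA is planned, and dropout is compared between arms. A graph would reveal the pattern in Step 1. None of these handles missing visits, and none is stated to give a DASH contrast at 1 year.
- **The bias is conditional.** A reader might infer that the method always rewards the arm that starts worse, or that any missing late visit biases the comparison. Neither follows. The reversal needs converging arms. The false positives need a curved recovery and a sizeable imbalance in loss. The article gives no evidence of a 15- or 20-point imbalance and expects routine clinic visits to limit missing data.
- **Lack of weighting is inferred** from silence, and an analysis plan not shown here could supply it. This is fair, and that part is worded conditionally.

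A reader might also count clinic-only collection ("All clinical and outcome data will be collected in the outpatient clinic") as part of the fault. It is an operational choice and not an analysis error, so no change to it is asked for here.

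**Conclusion.** The point holds in a conditional form, as something that should be fixed. What is certain from the text and algebra is that the stated method compares gradients, that any constant difference between arms gives zero slope difference, and that it therefore cannot answer the article's own question about 1 year.

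What rests on assumption is the size of the missing-data bias: about 9–22% false positives at 5% v 20% missing and 12–29% at 10% v 30%, against about 5% with equal loss and 5–7% at 5% v 10%. Curved recovery is assumed, but it is plausible from *Background*, which reports union under bracing at 7.5 to 11.5 weeks with most daily activities restricted until then. The 6-week visit, where the fitted line begins, falls before that range.

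**What to change.** For DASH and the other repeatedly measured continuous outcomes, replace the gradient comparison, both as the inferential method and as the missing-data rule, with a mixed model for repeated measures. Include visit as a category, treatment, treatment-by-visit, the age stratum used in randomisation, and pre-injury DASH where available. Report the adjusted between-arm difference with 95% CI at each visit, including 1 year, and state the missing-at-random assumption. The model uses participants with partial follow-up, imposes no straight line, and weights incomplete records according to the information they carry. Individual slopes can stay as description.

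The cost is a change of wording in two sections and slightly more analysis work. The sample size stays at 70 and the 3-month primary test is unchanged.

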### Health economic analysis

Direct costs of the injury and its treatment will be assessed, including the costs for any of the following:plaster or brace immobilisationany surgical procedure (including implant costs, theatre time, hospital admission and treatment of early complications)analgesia or other treatments for ongoing pain or other complications (pharmaceutical or otherwise)any additional clinical input (including primary and secondary care encounters and re-admissions to hospital)any allied health professional input (including physiotherapy and occupational therapy)any occupational or statutory sick pay received during employment absence

Secondary costs will also be assessed, including:any loss of earningsany additional support required for patients to complete their activities of daily living or to fulfil their own caring responsibilities to others

These data will allow an analysis of the overall economic impact of humeral shaft fractures and a comparison of the cost implications of each treatment strategy. A cost per quality-adjusted life year (QALY) gained will be calculated (total cost difference between treatment groups / difference in QALYs between treatment groups). QALYs will be calculated at 1 year, using the difference between the EQ-5D scores at the follow-up intervals.

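### The stated QALY rule uses differences between EQ-5D scores with no weighting by time, which as written measures change in utility, not QALYs

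*Protocol article*

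**What the plan says.** The Health economic analysis section defines cost per QALY gained as "total cost difference between treatment groups / difference in QALYs between treatment groups". The next sentence says how the QALYs themselves are obtained: "QALYs will be calculated at 1 year, using the difference between the EQ-5D scores at the follow-up intervals". It mentions neither weighting by time nor an area under a curve. Outcome assessment places follow-up at "outpatient clinic visits at 2 weeks, 6 weeks, 3 months, 6 months and 1 year", so the intervals between visits are very unequal. The Missing data section handles gaps at other timepoints by comparing fitted slopes, which is again a rate of change and not an area.

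On costs, the direct list includes "any occupational or statutory sick pay received during employment absence". Lost earnings appear separately among secondary costs. The article does not define total cost or say whether lost earnings are net of sick pay.

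**The concern.** A difference between two scores has no time unit. If successive differences are summed across visits, the intermediate scores cancel and only last minus first remains. A patient who recovers by 6 weeks and one who recovers by 11 months then receive the same value if they start and finish level.

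This matters because the trial's primary question is about early function, at 3 months, and the 1-year visit is there to see whether any difference lasts. A benefit concentrated early in the year is therefore one plausible result, and it is the kind that a change score fails to register. The denominator of the cost per QALY could be near zero or have the wrong sign while patients in one arm had spent months in better health.

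On costs, sick pay replaces wages. If it is added to the full wage lost, the same loss enters twice.

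**Working it through.** **What can be reproduced.** The article gives no utility, QALY or cost figure. Its one reproducible design figure is the sample size: 2 × (1.960 + 1.282)² × 12² / 10² = 30.3, so 31 per arm; 31 / 0.9 = 34.4, so 35 per arm and 70 in total (an exact t-test calculation gives 36 per arm). It plays no part in what follows. Every utility and cost below is an assumption chosen to show how the rule behaves.

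**Inputs.** Times are 0, 2, 6, 13, 26 and 52 weeks: the listed visits plus an assumed baseline. Assumed utilities:
- surgery: 0.30, 0.50, 0.65, 0.75, 0.80, 0.85
- brace: 0.30, 0.40, 0.50, 0.62, 0.75, 0.85

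**Area under the curve.** QALYs = Σ (uᵢ + uᵢ₊₁)/2 × (weeks in interval) / 52.
- surgery: (0.80 + 2.30 + 4.90 + 10.075 + 21.45) / 52 = 39.525 / 52 = 0.760
- brace: (0.70 + 1.80 + 3.92 + 8.905 + 20.80) / 52 = 36.125 / 52 = 0.695
- gain: 3.400 / 52 = 0.065 QALY

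**Change score.** (0.85 − 0.30) − (0.85 − 0.30) = 0, so the ratio is undefined.

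**If the first EQ-5D is at 2 weeks.** Area gain over weeks 2 to 52: (38.725 − 35.425) / 52 = 0.063. Change score: (0.85 − 0.50) − (0.85 − 0.40) = −0.10. The early benefit now counts against surgery.

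**Other assumed curves**, all against a brace curve of 0.30, 0.40, 0.50, 0.65, 0.78, 0.85 (area 0.712) and with an assumed extra cost of 3000:

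| Surgery curve | Area gain | Change-score gain | Cost per QALY, area | Cost per QALY, change score |
|---|---|---|---|---|
| 0.30, 0.50, 0.65, 0.75, 0.80, 0.85 (level at 1 year) | 0.048 | 0.000 | about 62,000 | undefined |
| 0.30, 0.50, 0.65, 0.75, 0.82, 0.87 (ahead by 0.02) | 0.061 | 0.020 | about 49,000 | 150,000 |
| 0.30, 0.40, 0.60, 0.75, 0.80, 0.84 (behind by 0.01) | 0.035 | −0.010 | about 86,000 | negative |

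Two arms constant at 0.70 and 0.60 all year differ by 0.10 QALY by area and by 0 by change score.

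**The valid alternative reading.** Suppose the sentence means the between-arm difference at each visit, integrated over time. In the first illustration these differences are 0, 0.10, 0.15, 0.13, 0.05 and 0. The trapezoid gives (0.10 + 0.50 + 0.98 + 1.17 + 0.65) / 52 = 3.40 / 52 = 0.065, identical to the difference in areas.

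**Costs.** Assume a wage of 500 a week and 4 weeks' difference in absence: wage loss 4 × 500 = 2000. Let sick pay replace a share s of wages.
- sick pay + gross lost earnings = 2000 × (1 + s): 2400, 3000 and 4000 for s = 20%, 50% and 100%
- sick pay + net lost earnings = 2000s + 2000(1 − s) = 2000 in every case

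**The case against.** The strongest reply is that this is one loose sentence in a condensed article. It is silent on time and does not reject the area method. The plural reference to intervals fits poorly with a simple last-minus-first change, and if the differences are between arms and carried across the intervals, the answer is exactly right, as shown above. Computational detail may sit in the full protocol or analysis plan.

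Part of this stands: the sentence does not prove that the final figure will be wrong. But the article does not leave the method open; it states one. The sentence before it already subtracts one group's QALYs from the other's, so this sentence must describe the QALYs before that subtraction; the between-arm reading would take the difference twice. It also needs an integration step that is not stated.

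On costs the reply is stronger. Lost earnings listed apart from sick pay may well mean income actually lost, in which case the two items add up correctly. A reader might infer that both halves of the ratio are wrong. The text does not support that: double counting requires both items to enter an undefined total and earnings to be recorded gross. Sick pay under direct costs is an odd label, since it is a payment between parties, but not by itself an error in the total.

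It is also fair to say that the zero gain is built into utilities assigned equal start and end points.

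**Conclusion.** The QALY rule needs correcting. On its natural reading it is not a QALY calculation. Under the assumed curves it turns an area gain of 0.035 to 0.065 QALY into zero, about one third of the true gain, or a loss. The mechanism does not depend on those values, but the size in this trial is unknown because the documents give no utilities.

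Two further inferences are not supported. The article nowhere says that the arms will converge by 1 year; its null hypothesis is no difference at 3 months. Nor does it say that work absence differs by arm; return to work is an outcome under test.

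The cost point is conditional only: under the assumptions above, an overstatement of 20% to 100% of the wage loss if earnings are gross and both items are totalled, and none if earnings are net. All of this bears on a secondary analysis and leaves the primary outcome and sample size untouched.

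**What to change.** Replace the QALY sentence with one to this effect: each participant's QALYs are the time-weighted (trapezoidal) area under the EQ-5D utility curve over all EQ-5D assessments to 1 year, adjusted for baseline utility if a baseline EQ-5D is collected; the between-arm difference in these is the denominator of the cost per QALY.

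Add one sentence on work loss: either lost earnings are recorded net of sick pay and both items are totalled, or earnings are recorded gross and sick pay is left out of the total. One or the other, not both, since net earnings without sick pay would understate the wage loss.

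The cost is two sentences and no new visits. Follow-up EQ-5D and both cost items are already planned. Whether a baseline EQ-5D is taken cannot be checked here, because the schedule figure is not shown; if it is not, state how the time before the first assessment is handled.

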### Patient involvement, safety and confidentiality

Patient and public involvement was not sought for this small, single-centre trial.

The maximum possible radiation dose for study participants is equivalent to 2 weeks of the dose to the UK population from natural sources of background radiation. The risk of fatal cancer arising from this level of exposure is negligible, at 1 in 230,000 [34]. This proposed radiation exposure has been approved by a medical physics expert and a consultant radiologist.

Complication rates will be monitored by study investigators throughout the trial, but a formal data monitoring committee will not be convened. Both treatment options (operative and non-operative) are regularly employed in the study centre, and any additional risk to patient safety is low. The study sponsor will be regularly updated with study progress and any patient safety issues that may arise, including adverse or serious adverse events. The trial steering committee will be consulted if required. The procedure for identifying, recording and reporting adverse events and urgent safety measures will adhere to relevant guidelines from the study sponsor, which will also advise upon any action required to protect patient safety.

Data collection forms will be kept in a secure filing cabinet in the research office on the study site, both of which are locked when not in use by the study investigators. These personal data will then be entered and stored electronically, under a password-protected file on a password-protected NHS computer system and will be accessible only by the study investigators. Once data collection is complete and analysis begins, non-personal data (stored using unique participant numbers rather than names or other identifiable information) will be made available to other authorised members of the research team. All electronic data will be handled according to study sponsor guidelines on data protection and confidentiality.

When finalised, study results will be disseminated via an internal report, conference presentations and peer-reviewed scientific journals. A summary of the results will be made available to study participants upon request.

## Discussion

A review of the existing literature indicates that there is a paucity of level 1 evidence to support operative management as the primary treatment for humeral shaft fractures. Several studies have retrospectively compared humeral shaft fracture outcomes following non-operative and operative management. Jawa et al*.* compared complication rates for distal-third humeral shaft fractures treated with bracing versus those treated with ORIF, concluding that both strategies had potential risks and that the optimal treatment was based on patient preference [35]. More recently, Denard et al*.* demonstrated that there was an increased likelihood of both nonunion and malunion with bracing, and in the context of comparable (or lower) complication rates with ORIF, concluded that ORIF should be performed more frequently [36]. Mahabier et al*.* also suggested there was little difference between non-operative and operative treatment in terms of fracture union or nerve injury [37].

In the only published randomised controlled trial of which the authors are aware, Matsunaga et al*.* compared bracing with a less widely employed minimally invasive bridge plating technique, demonstrating a statistically (but not clinically) significant difference in the DASH score in favour of the fixation group, along with significantly lower rates of nonunion, contact dermatitis and coronal plane malalignment at 6 months in the fixation group [38]. There was no significant difference in the DASH score at any other timepoint, and no difference in any other functional outcomes between the groups. However, this study did not assess the current gold standard surgical technique of compression plating and included a population substantially younger than the average patient sustaining a humeral shaft fracture in the UK [1].

Two ongoing randomised controlled trials comparing surgical fixation against functional bracing are currently recruiting patients, one in Canada (ClinicalTrials.gov ID NCT00878319) and one in Finland (ClinicalTrials.gov ID NCT01719887) [39]. A further prospective multi-centre observational study comparing functional recovery after operative versus non-operative treatment is also underway in the Netherlands (Netherlands Trial Register ID NTR3617) [40]. The HU-FIX study aims to contribute to this growing body of literature and provide greater clarity to surgeons managing patients with humeral shaft fractures.

The study is pragmatic and allows for normal variations in clinical practice, including in the surgical approach and fixation method used during ORIF, as well as the involvement of physiotherapy. The investigators hope that this pragmatic design will reproduce day-to-day trauma care and improve the external validity of study results [41, 42]. Potential limitations include the single-centre study design and the lack of blinding. Edinburgh Orthopaedic Trauma provides trauma care to a catchment population of approximately 850,000 and consists of 12 consultant orthopaedic trauma surgeons who collectively treat approximately 70 humeral shaft fractures per year [1]. The investigators are, therefore, confident that the study results can be reliably extrapolated to the wider orthopaedic community. Patient blinding is not possible in this study given the nature of the interventions being compared, neither is assessor blinding, as the presence or absence of a surgical scar or metalwork on plain radiographs will be obvious during outcome assessment. Again, this is consistent with a pragmatic design that reflects everyday clinical practice. Although this study is not a pilot for a larger multi-centre randomised controlled trial, the investigators hope that the results of the HU-FIX Study will inform researchers planning or preparing a multi-centre trial in the future.

Use of patient-reported measures to assess outcomes after a traumatic injury is consistently expanding [43], with the main advantage being that determining injury outcome or treatment success is increasingly becoming patient-centred. The DASH score is a holistic measure of outcome, assessing impairment, activity limitation and participant restriction [44]. However, it does not distinguish between the injured and uninjured limbs, which may artificially inflate scores for patients who are more able to compensate for the loss of function in one limb (e.g. young active patients with injuries to their non-dominant arm). It is, therefore, important to adjust for these potential confounding factors during statistical analysis.

